## Discussion

The purposes of the trial are to determine the effectiveness of acupuncture for the treatment of insomnia disorder and explore the potential neural mechanisms by which acupuncture affects sleep quality using neuropsychological measurements and rs-fMRI methods.

Based on the hyperarousal hypothesis, we will investigate the effect of acupuncture on spontaneous activities and functional connections in abnormal brain regions. The hyperarousal state was not assessed with fMRI analyses in previous clinical trials. To the best of our knowledge, this is the first randomized controlled trial associating the effects of acupuncture on insomnia disorder with its effects on brain hyperarousal state measured with rs-fMRI methods. The trial will provide important data on the effect of acupuncture and its possible mechanistic associations.

The influence of acupuncture on spontaneous regional brain activity and functional connectivity in patients with insomnia disorder will be explored using ALFF, ReHo, and functional connectivity analyses. ALFF [35] and ReHo analyses are simple, easily implemented methods which exhibit favorable test–retest reliability and have been successfully applied to insomnia research. Increased information processing in the emotion-related regions, manifested as higher ReHo and ALFF scores, suggest an association with the hyperarousal state of insomnia disorder [13–16]. However, the results of the previous studies have not been consistent enough to yield any general conclusions. Thus, we included a healthy control group. Baseline ReHo and ALFF values and functional connectivity maps from the patients with insomnia and the healthy control group will be compared to explore the characteristics of brain regions in patients with insomnia disorder.

In a recent study, acupuncture therapy decreased hyperarousal level and improved sleep quality in patients with insomnia disorder [9]. We speculate that this effect may have relevance to the modulation of regional brain activity and functional connectivity, especially in emotion-related areas. If our hypothesis is correct, ALFF and ReHo values and functional connectivity maps of the emotion-related regions will be modulated more in the group receiving acupuncture than in the sham group. These results will provide insight into the potential intrinsic mechanism of acupuncture for treating insomnia disorder.

Long-term effectiveness is an important feature of the ideal treatment for insomnia. We found that verum acupuncture exhibited long-term effects in the follow-up period compared with sham acupuncture in patients with insomnia [23]. The possible neurobiological basis of the long-term effects is not well understood. Acupuncture may induce a long-term regulatory effect on brain function. In our trial, all patients will undergo fMRI during the follow-up period. One of the greatest strengths of the present study is the investigation of the long-lasting effects of acupuncture on insomnia and the central mechanism of the long-term effects of acupuncture.

Actigraphy will be applied in our trial to assess the changes in sleep quality. Although actigraphy may not be as accurate as polysomnography, this method can provide an accurate estimate of typical sleep duration. Actigraphy is more accepted and well tolerated by patients with insomnia disorder. Furthermore, actigraphy can record sleep in the patients’ natural environment and decreases the interference of factors that change a patient’s characteristic sleep patterns [36]. Meanwhile, sleep diaries and questionnaires will be recorded at the same time as the actigraphy. At follow-up, rs-fMRI and actigraphy analyses will be performed to provide objective measures related to the long-term alterations of sleep quality and brain function in insomnia disorder.

The design of an appropriate control group for a clinical trial is critical. However, it is difficult to use placebo needles for controls. Thus, we will use acupoints in the sham acupuncture group that are considered ineffective for insomnia according to our clinical experience. The possible nonspecific physiological reactions induced by needle pricking will be minimized by superficial puncturing and no manipulation to avoid the De qi sensation, which is believed to be fundamental to the efficacy of acupuncture.

The acupuncturists will receive training for consistent practices, including acupuncture point location and manipulation, to achieve effective quality control.

Despite the measures taken to ensure a well-controlled trial, there are several methodologic limitations to this study. First, the treatment intervention duration of 4 weeks may be insufficient to achieve a measurable response, and a prolonged treatment period may result in a better effect. Second, there is no insomnia subgroup design. According to the definition of psychophysiological insomnia, this subtype has more relevance to the hyperarousal state with learned sleep-preventing associations [37].. Other subtypes such as paradoxical insomnia and adjustment insomnia may have lower levels of hyperarousal. In our study, the insomnia disorder inclusion criteria of a “score above 32 on the HAS” will ensure the degree of hyperarousal. In further research, subgroup design and prolonged treatment periods should be considered when investigating the efficacy of acupuncture in treating insomnia. With the improvements in fMRI techniques, further advances can be made to clarify the neural substrates underlying the effects of acupuncture in insomnia disorder. In spite of its limitations, we hope our trial will help to provide new insights into the central neurological basis of acupuncture for treating insomnia disorder.

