### Trial design

This study will be conducted as a single-center, prospective parallel group, patient- and assessor-blinded, randomized controlled trial. The trial will be conducted in accordance with the Consolidated Standards of Reporting Trials [18] and Standards for Reporting Interventions in Clinical Trials of Acupuncture principles [19] to fulfill adequate reporting standards for randomized controlled trials. Sixty patients with insomnia disorder will be assigned to either a real acupuncture group or a sham acupuncture group, using a digital randomization table in a 1:1 ratio. Participants will keep a sleep diary at baseline, during week 4 of treatment, and during week 8 of the follow-up period. Both the neuropsychological measurements and fMRI scans will be performed at baseline, after completion of the acupuncture treatments, and at the conclusion of the follow-up period. Thirty age- and sex-matched healthy individuals who sleep well will be recruited as controls for the fMRI data analysis. All outcome measures will be performed once for the healthy control patients (Fig. 1).

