#### HAMD and HAMA

Assessment of depressive status will be made with the HAMD. The HAMD is comprised of 17 variables with five- or three-point scales. Scores will be interpreted as follows: less than 7, normal; 8 to 17, mild depression; 17 to 24, moderate depression; and 24 or over, severe depression [31].

The 14-item HAMA will be used to determine anxiety. The HAMA is comprised of a 14-point self-assessment questionnaire, with a five-point scale for each item. A normal score is less than 7, scores between 7and 14 suggest mild anxiety, scores between 14 and 20 indicate moderate anxiety, scores between 21 and 28 indicate severe anxiety, and a score greater than or equal to 29 indicates extremely severe anxiety [32].

For patients with insomnia disorder, the scores for HAMD and HAMA will be collected at baseline, week 4, and at the 8-week follow-up. The HAMD and HAMA will be collected only once at baseline in the healthy control group. Collection of the week-long sleep diaries will be at baseline, at 4 weeks after treatment, and at the end of the 8-week follow-up.

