#### Functional MRI data analysis

The fMRI data will be analyzed with SPM12 software (Wellcome Department of Imaging Neuroscience, London, UK), MATLAB_R2018a (Mathworks, Inc., Natick, MA, USA), DPARSF_V2.2 (http://www.rfmri.org/DPABI), and Freesurfer (http://surfer.nmr.mgh.harvard.edu/) software. Original data will be corrected; slice timing, affine head motion, and nonbrain extraction, spatial smoothing and temporal filtering will be applied.

Baseline ReHo and amplitude of low-frequency fluctuations (ALFF) values and functional connectivity maps from the real and sham acupuncture groups and the healthy control group will be compared using independent *t* tests. Independent *t* tests will be used for comparison of ReHo or ALFF values from the two groups after acupuncture. Paired *t* tests will be used to compare the pre-acupuncture and post-acupuncture data within each group. Average time series data from significant areas will be extracted to test the regional relationship with the rest of the brain using voxel-based general linear modeling. Fisher’s R-to-Z transformation will be applied to compare resting state functional connectivity using independent-sample *t* tests between groups [34].

Pearson’s correlation analyses will be performed to evaluate the relationship of clinical symptoms with ReHo or ALFF values in regions demonstrating significant differences between groups.

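### Healthy controls have no limits on the mood or sleep scales that patients must meet, which could blur the exploratory baseline imaging contrast (minor, cheap to improve)

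*Protocol article*

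**What the plan says.** **Patients.** The protocol article's inclusion criteria for patients set four score limits: PSQI above 8, HAMD below 7, HAMA below 14 and HAS above 32. The Discussion says of the HAS limit that it "will ensure the degree of hyperarousal".

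**Controls.** Under Trial design, "Thirty age- and sex-matched healthy individuals who sleep well will be recruited as controls for the fMRI data analysis". Their inclusion criteria ask for no complaint about sleep, age 20 to 60, consent, and a month without medication for anxiety, depression or insomnia. Their exclusion criteria work by diagnosis, for example of depression, anxiety or another sleep disorder. No score on any scale appears in either list.

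**Measurement.** The scales are nevertheless taken in controls. Trial design states "All outcome measures will be performed once for the healthy control patients", and the section on HAMD and HAMA adds "The HAMD and HAMA will be collected only once at baseline in the healthy control group".

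**Analysis.** Baseline ReHo, ALFF and connectivity maps "from the real and sham acupuncture groups and the healthy control group will be compared using independent" t tests, with no covariate named. The Discussion repeats that "Baseline ReHo and ALFF values and functional connectivity maps from the patients with insomnia and the healthy control group will be compared", and the stated aim is "to explore the characteristics of brain regions in patients with insomnia disorder".

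**The concern.** The Discussion explains that earlier imaging results were too inconsistent to support general conclusions, and that the healthy group was added for that reason. The baseline contrast is therefore the main use of these 30 people, and it helps if the two groups differ in insomnia and as little as possible in anything else.

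Mood is the obvious other factor. The trial targets emotion-related regions, and the Background cites an imaging study in which ReHo in the left insula rose with self-rated anxiety. By the protocol's own account, then, mood is a correlate of the imaging measure. It is capped by score in patients but only by diagnosis and medication in controls. A control group with subthreshold depressive or anxiety symptoms would bring that correlate into the comparison. A control who scores as a poor sleeper would overlap the patient definition and pull the difference towards zero.

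**Working it through.** **Criteria side by side.**

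| Scale | Patients | Controls | What the control criteria still permit |
|---|---|---|---|
| HAMD | below 7 | none | 7 or more, above every patient |
| HAMA | below 14 | none | 14 or more, above every patient |
| PSQI | above 8 | none | above 8, inside the patient range |
| HAS | above 32 | none | above 32, inside the patient range |

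Four of four scales are limited in patients and none of four in controls.

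**HAMD.** The protocol's bands are "less than 7, normal; 8 to 17, mild depression". A volunteer scoring 10, with no diagnosis and no medication, breaks no control criterion. The same score bars a patient.

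**PSQI.** A score above 8 is possible on paper but harder to reach. Five of the seven components (quality, latency, duration, efficiency, disturbances) ask about the very problems this person says they do not have, and a sixth, sleeping medication, is largely closed by the medication criterion.

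**Direction.** If mood raises the regional measure, higher mood scores in controls would shrink the patient-control difference and lower ones would enlarge it. The protocol classes HAMA 7 to 14 as mild anxiety, so the patient limit itself admits mildly anxious patients. Imbalance could run either way.

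**Size of dilution (illustration only).** The plan gives no figure to reproduce. Suppose the true difference is d standard deviations and a share f of controls has the full patient value on the imaging measure. Both are assumptions. Then:

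- expected difference = d(1 − f)
- control variance = 1 + f(1 − f)d²
- power ≈ Φ(difference / SE − 1.96), with SE = √(control variance/30 + 1/n), where n = 30 (one arm against controls) or 60 (both arms pooled); the text permits either reading.

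For d = 0.8 and f = 0.2: the difference is 0.8 × 0.8 = 0.64, and the control variance is 1 + 0.2 × 0.8 × 0.64 = 1.1024. With n = 30, SE = √(2.1024/30) = 0.265 and power is Φ(2.418 − 1.96) = 0.676.

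| d | Patients v controls | f = 0 | 0.1 | 0.2 | 0.3 |
|---|---|---|---|---|---|
| 0.5 | 30 v 30 | 0.491 | 0.410 | 0.335 | 0.267 |
| 0.5 | 60 v 30 | 0.609 | 0.515 | 0.423 | 0.337 |
| 0.8 | 30 v 30 | 0.873 | 0.785 | 0.676 | 0.555 |
| 0.8 | 60 v 30 | 0.947 | 0.885 | 0.791 | 0.670 |

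These values describe the assumption, not the trial. They give every high-scoring control the complete patient value and treat a whole-brain map as one 5% test.

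**The case against.** The best defence is that controls are screened already. They must sleep well and make no complaint, and diagnosed or recently medicated anxiety and depression are excluded, so high scores should be uncommon. This stands as to likelihood, but it sets no limit. The recruitment section has a neurologist score the scales to check inclusion criteria; that does not close the gap, because the control criteria contain no score to check.

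Second, the contrast is exploratory. None of the stated hypotheses involves controls; all compare real with sham. This stands and governs the severity.

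Third, a reader might infer that a difference in amygdala or insula measures, or its absence, could not be attributed to insomnia at all. The documents do not support that. The scores are recorded in controls, so imbalance will be visible and can be adjusted for or tested, and an analysis plan not shown here may say how.

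Fourth, a reader might want a HAS ceiling for controls to mirror the patient floor. The HAS floor is discussed in relation to insomnia subtypes among patients, while the contrast is described as insomnia against healthy sleepers. Patients above 32 and controls at or below 32 would be separated by construction on a correlate of the imaging measures, which can exaggerate the difference. That objection stands.

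It is not a sufficient answer that an article condenses its protocol. Both eligibility lists are itemised, and the control list repeats the age, consent and medication items while omitting the score line.

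**Conclusion.** The asymmetry is real and stated in full: score limits on four scales for patients and none for controls. The clearest case is a control with HAMD 8 to 17; HAMA of 14 or more is also open, and PSQI above 8 is open but less plausible. Confounding or dilution of the baseline patient-control contrast is therefore possible. It depends on such volunteers actually being enrolled, and its direction is uncertain.

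A reader might take the power table as a forecast of loss. It is not one, because the documents give neither d nor f and the size cannot be estimated from them. The randomised comparisons of real with sham, including the primary PSQI outcome, do not depend on who the controls are. This is a minor point and a cheap improvement.

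**What to change.** 1. In the inclusion criteria for healthy controls, add HAMD below 7 and HAMA below 14, as for patients, and PSQI not above 8.
2. For any control already scanned outside these limits, run the baseline contrast with and without that person.
3. Do not make HAS an eligibility rule for controls. Report their HAS scores and examine them in a sensitivity analysis.

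Equal limits do not guarantee equal distributions. Patients may still be more anxious than controls within HAMA below 14, so both groups' baseline scores should be shown beside the imaging result.

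The cost is an amendment to one list, scoring the scales before the scan, and a few volunteers turned away. No new instrument is needed, because controls complete these scales already. The Trial status section reports six participants recruited at submission, so at that point few controls, if any, could have been affected.

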## Trial status

The Medical Ethical Committee of the Beijing Hospital of Traditional Chinese Medicine approved the study protocol on 12 March 2018 (permission 2018BL-002-02 for protocol 20,180,209). This trial was registered in March 2018 (ChiCTR1800015282). Due to the time required for recruitment and preparation, the trial started in November 2018. The first participant was included in January 2019, and six participants have been recruited as of the date of this submission. The trial is currently recruiting participants. We predict that recruitment will be completed by November 2020.

## Data Availability

All study-related data will be stored securely at the Beijing Hospital of Traditional Chinese Medicine. The datasets analyzed during the current study are available from the corresponding author for a future secondary analysis.

## Abbreviations

ALFF: Amplitude of low-frequency fluctuations
FS-14: Fatigue scale-14
HAMA: Hamilton anxiety scale
HAMD: Hamilton depression scale
HAS: Hyperarousal scale
PSQI: Pittsburgh Sleep Quality Index
ReHo: Regional homogeneity
rs-fMRI: Resting state functional magnetic resonance imaging
